## Abstract

**Background:** Sports-related concussion (SRC) is a complex injury with heterogeneous presentation and management. There are few studies that provide guidance on the most effective and feasible strategies for recovery and return to sports participation. Furthermore, there have been no randomized studies of the feasibility, safety, and efficacy of early rehabilitation strategies across multiple sports and age groups. This international cluster-randomized pragmatic trial evaluates the effectiveness of early multi-dimensional rehabilitation integrated with the current return to sport strategy vs. the current return to sport strategy alone.

**Methods:** The study is a cluster-randomized pragmatic trial enrolling male and female athletes from 28 sites. The sites span three countries, and include multiple sports, levels of play (high school, college, and professional), and levels of contact. The two study arms are Enhanced Graded Exertion (EGE) and Multidimensional Rehabilitation (MDR). The EGE arm follows the current return to sport strategy and the MDR arm integrates early, MDR strategies in the context of the current return to sport strategy. Each arm employs a post-injury protocol that applies to all athletes from that site in the event they sustain a concussion during their study enrollment. Participants are enrolled at pre-season baseline. Assessment timepoints include pre-season baseline, time of injury (concussion), 24–48 h post-injury, asymptomatic, and 1-month post-injury. Symptoms and activity levels are tracked post injury through the return to play process and beyond. Injury and recovery characteristics are obtained for all participants. Primary endpoints include time to medical clearance for full return to sport and time to become asymptomatic. Secondary endpoints include symptom, neurocognitive, mental status, balance, convergence insufficiency, psychological distress, and quality of life trajectories post-injury.

**Discussion:** Outputs from the trial are expected to inform both research and clinical practice in post-concussion rehabilitation across all levels of sport and extend beyond civilian medicine to care for military personnel.

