#### Guided Rest + Enhanced Graded Exertion (EGE Arm)

Participants in the EGE arm complete the activities described above and guided rest prior to progressing past Stage 1 of the graded exertion (Table 1) (16). The term EGE was chosen as sites are directed to be sports specific in their choice of activities throughout the progression. A medical professional determines the symptom status of the athlete and when Stage 2 of the graded exertion for return to sport will begin. Once the athlete has been asymptomatic for 24 h (within at least 85% of their baseline symptom score—definition of asymptomatic for the study) they may begin the EGE progression. This protocol follows the 5th International Consensus Statement on Concussion in Sport return to sport strategy (16), but encourages enhancement to include sports and skill specific activities. Each step is recommended for completion on a separate day, at the clinician's discretion. Clinicians complete session logs for each graded exertion session for Stage 2 and for subsequent stages that include the following information: initial symptom checklist, phase of graded return to play progression, specifics on session activities, percentage of rest during the session, participants rating of perceived exertion, final symptom checklist, session satisfaction rating, and overall session feedback.

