#### Guided Rest + Multidimensional Rehabilitation + Enhanced Graded Exertion (MDR Arm)

The term MDR was chosen to illustrate more than one area of activity would/could be addressed. Participants in the MDR arm complete the same activities as the EGE arm participants (as described above). However, once the participants' symptoms become “stable” (i.e., not getting worse), they are progressed into the MDR activity phases. “Stable” is defined as no significant increase utilizing Reliable Change Indices (RCI) metrics [symptom score not increasing by 10 or more over a 24-h period from their initial (first) symptom assessment] and no significant development of new symptoms over 24 h. Prior to beginning the exercises in the intervention, clearance to do so is obtained and documented by the athlete's healthcare team. The intervention includes 5 progressive phases: symptom control, perceived impairment reduction, activity integration, recovery acceleration, and sport specific application (Figure 2).

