### Study Outcomes and Assessments

The primary trial endpoints include time to asymptomatic/symptom free and time to full clearance for return to sport, in days. The secondary endpoints include clinical and quality of life outcomes assessed from baseline through 1-month post return to play, as well as safety and feasibility outcomes. An assessment protocol similar to the NCAA-DOD Grand Alliance Concussion Assessment, Research, and Education (CARE) Consortium's is utilized for both baseline measurements and post-injury assessments and to achieve the primary and secondary endpoints (15). The assessment time-points for the study (Table 3) include: pre-season baseline, time of injury (optional, 24–48 h following injury, daily symptom and activity tracking through 7 days post-return to play, athlete satisfaction at 7 days post-return to play, and 1-month following full return to play. Each of the assessment timepoints are collected at the approximate windows, i.e., within 5 days, due to the nature of athletic schedules. Study measures are administered by trained site personnel and clinicians. Assessments take place at site medical and training facilities. Below are brief descriptions of all study measures.

**Table 3 T3:** Assessment schedule.

	**Demographics**	**Personal and family history**	**SCAT symptom checklist**	**QOL**	**BSI-18**	**Neurocognitive assessment**	**SAC**	**BESS**	**NPC**	**Dual-task**	**Start and end fatigue rating**
**Pre-season baseline**	✓	✓	✓	✓	✓	✓	✓	✓	✓	✓	✓
**Time of injury (within 6 h—if possible)**			✓				✓	✓			
**24–48 h post-injury**			✓		✓	✓	✓	✓	✓	✓	✓
**Asymptomatic post-injury**			✓	✓	✓	✓	✓	✓	✓	✓	✓
**1-month post return to play post-injury**			✓	✓	✓	✓	✓	✓	✓	✓	✓
- Symptoms and activity assessed daily from the first assessment point until 7 days post return to play - Concussion Index completed following injury - Recovery Form completed following return to play - *Participant Satisfaction completed at 7-days post return to play*											

*QOL, Quality of Life; BSI-18, Brief Symptom Inventory 18 item; SAC, Standardized Assessment of Concussion; NPC, Near Point of Convergence; SCAT, Sport Concussion Assessment Tool*.

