***Specific Aim 1***
*(evaluation of effectiveness):* For analyses of our primary endpoints, Cox proportional hazards regression models (35) will be used to compare time to return to play and time to asymptomatic between the EGE and MDR groups. The specific outcomes for the Cox models will be time from date of injury to: (1) date of medical clearance for full return to participation and (2) asymptomatic date. The Wei-Lin robust variance estimator will be used to account for the effect of cluster-randomization by site (36).

For our secondary endpoints (clinical and quality of life measures), recovery trajectories will be examined by use of General Linear Mixed regression models and non-parametric smoothers. Random effects will be utilized to account for the effect of clustering by site and the effect of repeated observations over time within an individual participant. The time axis to be modeled in both sets of analyses is time from initiation of the treatment (defined as stable symptoms for 24 h), and time will be treated as a continuous variable in all analyses.

We will also assess potential predictors of attrition (e.g., gender, race, socioeconomic status). If no predictable patterns are observed for missing data (i.e., missingness occurs at random), no imputations will be conducted. Inverse probability of attrition weights based on the factors influencing attrition will be used to account for potential selection bias due to attrition. We will assess the differences between the EGE and MDR group participants (those with SCR) at baseline and before starting the treatment protocol.

For sensitivity analyses of primary and secondary, we will conduct intent-to-treat analysis (prescribed treatment), per-protocol analysis (adhered treatment) and use inverse probability weighting to determine potential outcomes had everyone adhered to their prescribed treatments.

To test the effectiveness of randomization, we will compare key variables at baseline and immediately post-injury (24-48 h timepoint) to determine differences between arms. These variables at a minimum will include: age, gender, previous history of concussion, contact/collision sport, baseline symptom severity score, 24–48 h symptom severity score. Should any differences be observed these factors will be controlled for in the models. Additionally, 24–48 h symptom severity will be considered in all analyses.

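### Specific Aim 1 gives two time origins, injury and treatment start at stable symptoms; the second is ambiguous in scope and marks a treatment start in only one arm

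*Protocol article*

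**What the plan says.** All references are to the protocol article.

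- **Primary endpoints (Specific Aim 1, first paragraph).** "The specific outcomes for the Cox models will be time from date of injury to" the date of medical clearance and the asymptomatic date.
- **Time axis (Specific Aim 1, second paragraph).** After naming mixed models and non-parametric smoothers for the secondary endpoints, the text says "The time axis to be modeled in both sets of analyses is time from initiation of the treatment", which it explains as "defined as stable symptoms for 24 h". The sentence ends by saying that "time will be treated as a continuous variable in all analyses".
- **MDR arm.** Once symptoms are stable, "they are progressed into the MDR activity phases", after documented clearance by the healthcare team. Stability is a score rule: no rise of 10 or more points over 24 h from the first assessment, plus no significant new symptoms. Table 2 puts the earliest start at 24–48 h after injury and expects most athletes to qualify then.
- **EGE arm.** "Participants in the EGE arm complete the activities described above and guided rest prior to progressing past Stage 1". The graded progression opens after 24 h asymptomatic, and no step is tied to stable symptoms.
- **Allocation to Study Arm.** Site clinicians know their arm.
- **Last visit.** The Abstract lists "asymptomatic, and 1-month post-injury"; Study Outcomes and Assessments has "1-month following full return to play".

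**The concern.** A time-to-event comparison needs one time zero that means the same thing in both arms. Here the primary outcomes are defined from injury, and a later sentence can be read as resetting the clock for them too. Two analysts following the same text could then report different hazard ratios for both primary endpoints.

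On the narrower reading, only the secondary trajectories are affected. Their origin then comes after injury and is a treatment gate in MDR, but it corresponds to nothing that begins in EGE. MDR sites have a reason to record it, because exercise cannot start without it. EGE sites do not. If the recorded date falls systematically later in MDR, each MDR athlete's measured recovery is shortened without any treatment effect. A shift the other way would penalise MDR.

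**Working it through.** **1. The plan's own figure.** Schoenfeld power with 1:1 allocation and two-sided alpha 0.05 (assumed; the article states none) is Φ(|ln HR|·√d/2 − 1.96). For HR = 4.5/7, |ln HR| = 0.4418. With 100 per arm and 12.5% attrition (midpoint of the stated 10–15%), d = 200 × 0.875 = 175 and √175/2 = 6.614. Then 0.4418 × 6.614 − 1.96 = 0.962 and Φ(0.962) = 83.2%. At 180 and 170 events power is 84.2% and 82.1%. The stated 83% is reproduced. The formula contains no time origin, so fixing the origin leaves it unchanged.

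**2. Scale.** Table 4 implies about 7 days to asymptomatic in EGE. A pure clock shift of 1 or 2 days turns 7 into 6 or 5, giving 6/7 and 5/7, which are both effect sizes in Table 4.

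**3. Null simulation, time to asymptomatic.** There is no treatment effect, with 100 per arm and 500 runs. Recovery is Weibull (shape 1.5, mean 7 days), log-normal (median 7, log-SD 0.6) or exponential (mean 7). The stable date is uniform on days 1–2, plus a lag in MDR only. Athletes already asymptomatic at the origin are dropped. Distributions and lags are assumptions, and site clustering is not simulated. Entries are the Cox HR for MDR vs EGE (above 1 favours MDR), with the rejection rate at nominal 5%.

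| Origin | Weibull | Log-normal | Constant hazard |
|---|---|---|---|
| Injury | 0.997 (5.2%) | 0.995 (3.6%) | 0.994 (6.6%) |
| Stable, same timing | 0.990 (5.6%) | 1.003 (6.2%) | 1.003 (5.8%) |
| Stable, MDR +0.5 day | 1.053 (7.8%) | 1.075 (8.6%) | 0.991 (4.6%) |
| Stable, MDR +1 day | 1.100 (9.2%) | 1.136 (16.2%) | 1.010 (4.4%) |
| Stable, MDR +2 days | 1.189 (18.2%) | 1.246 (33.6%) | 1.017 (5.6%) |

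The planned effect, expressed in the same direction, is 7/4.5 = 1.56. On the log scale, 1.10 is 0.095/0.442 = 22% of it and 1.246 is 0.220/0.442 = 50%. Under constant hazard the HR is unbiased, but at +2 days 19% of EGE and 39% of MDR athletes are dropped.

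**4. Null simulation, time to clearance.** Clearance is taken as asymptomatic time plus an assumed 5–8 days, with 200 runs. A lag of 1 day gives HR 1.18–1.19 (rejection 21–23%), and 2 days gives 1.36–1.40 (55–64%). With equal timing HR is 1.01–1.02, but rejection is 8.0–9.5%. The simulation error of a 5% rate is √(0.05 × 0.95/200) = 1.5 points, so these rejection rates are rough.

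**5. Each arm's own treatment start as origin.** If EGE starts at asymptomatic plus 24 h and MDR at stable, median time to clearance is 5.5 days in EGE and 11–12 in MDR with no true effect. Time to asymptomatic is then −1 day for every EGE athlete. This shows that the phrase about treatment initiation cannot be applied literally in EGE.

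**6. Last visit.** The Abstract and the Recovery Tracking form anchor it at 1 month after injury. Table 3, the descriptions of most outcome measures and the sample-size paragraph anchor it at 1 month after return to play.

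**The case against.** The disputed sentence closes the secondary-endpoint paragraph, directly after two methods are named. The two sets of analyses may therefore be just the mixed models and the smoothers, and the closing reference to all analyses governs only the treatment of time as continuous. On that reading the primary origin is injury alone and no primary hazard ratio is touched. This stands as a possible reading. The text does not settle it, and the simulations above quantify Cox models, not trajectories.

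A reader might also infer that the stable-symptom origin is invalid in itself because it depends on arm. The article does not say so. Specific Aim 1 words the definition alike for both arms, daily symptom scores are collected in both, and the score rule can be computed identically. With the same rule and timing there is no bias in the hazard ratio. Nor is coming after randomisation the fault: sites are randomised before any injury, so injury comes after it too.

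Lags of 1 to 3 days confined to MDR might be taken as expected. They are assumptions. Table 2 expects most athletes to qualify at the earliest time, which points to small differences, and nothing supports a 3-day gap.

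Finally, an athlete who is recovering will usually meet the stability rule no later than recovery, and mixed models accept negative times, so large losses are not inevitable. What remains is that the article does not say how such athletes, or assessments within 6 h of injury, are placed on this axis.

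**Conclusion.** The point holds as a conflict, or at best an ambiguity, in the time origin. It is a contradiction if the sentence reaches the primary analyses. If it does not, the secondary trajectories rest on an origin that gates treatment in MDR only and may be judged by unblinded staff.

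Harm depends on the recorded date differing between arms. A 1 to 2 day difference, later in MDR, gives HR about 1.10–1.25 for time to asymptomatic under the Weibull and log-normal assumptions. It gives no HR bias under a constant hazard, and equal timing gives none at all. The size and direction of any real lag cannot be read from the article, so these figures show what the wording permits, not what will happen. The last-visit discrepancy is separate and mostly editorial.

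**What to change.** - State in Specific Aim 1 that date of injury is the single time zero for both primary Cox endpoints in both arms.
- Use the same origin by default for the mixed models and smoothers, entering the actual day since injury of each assessment.
- If a stable-symptom origin is kept for a secondary analysis, derive it from symptom scores by one rule applied identically in both arms. State how athletes already asymptomatic, and assessments before that origin, are handled.
- Reconcile the Specific Aim 1 definition of treatment initiation with the two arm descriptions.
- Use one label for the last visit in the Abstract, Recovery Tracking, Study Outcomes and Assessments, and the measure descriptions.

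The cost is wording only. The Concussion Injury Index already records injury date, no extra data are needed for the default, and the 83% power figure stays as it is.

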### Participants and Eligibility Criteria

The inclusion criteria for participants in the trial are individuals rostered as an athlete at the study sites who consent to the study. Written, informed consent is administered during a pre-season baseline assessment. Target participant enrollment across all settings is estimated to be 3,500 at baseline and 100–200 in each study arm (total *n* = 200–400) post-injury. The post-injury protocol includes all consented athletes with a SRC at each site and meeting the following criteria.

Our current trial aligns with common elements from the NCAA-DOD Grand Alliance Concussion Assessment, Research, and Education (CARE) Consortium (15). As such, we have defined SRC in accordance with the Department of Defense (DoD) operational definition as *a change in brain function following a force to the head, which may (or may not) be accompanied by temporary loss of consciousness (if LOC, temporary is defined as* <*30 min based on the Mayo TBI severity guidelines), but is identified in awake individuals with measures of neurologic and cognitive dysfunction, as indicated by 1 or more of the 22 symptoms from the Sport Concussion Assessment Tool (SCAT) symptom checklist* (16). No athlete with a Glasgow Coma Scale <13 enters the treatment progression of either arm.

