As is standard with SRC studies (15), identifying the SRC is determined by medical professionals at each site involving a physician and other team-based healthcare provider (based on clinical exam and their interpretation of objective findings inclusive of the definition above). If medically diagnosed with a SRC, and no other indicators of more moderate to severe TBI as defined in the Mayo definition above (17), consented participants are eligible for enrollment in the treatment protocol. Documentation of the clinical diagnosis and identification of the medical personnel making the diagnosis are recorded in study case report forms. For inclusion in the post-injury protocols, the SRC must occur in a rostered sport for a high school or collegiate sport at their school or for their specific rostered sport (and team sanctioned activity) for the professional cohort. Individuals with any positive/abnormal clinical neuroimaging finding(s) following injury are not entered into the post-injury protocol or are discontinued from their arm treatment protocol if these findings are observed after the protocol has been initiated. Although these individuals are discontinued from the treatment protocol, we continue to collect assessment time point data on these individuals and documentation for their overall care.

We anticipate ~10–15% attrition due to study demands and seasonal nature of sport through full clearance to return to sport. However, we expect 20–30% attrition for the 1-month timepoint due to this timing and other potential participant follow-up issues. The study protocol incorporates contacting participants to keep them engaged.

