**Figure 7 F7:**
[figure not shown]
Dual-task schematic. **(A)** Memory task begins, **(B)** walking task, and **(C)** memory recall.

**Daily Activity and Symptom Tracking**: All concussed participants complete a daily activity and symptom tracking survey (cognitive and physical) from time of injury through 7 days post return to play. The survey can be completed on paper or via Qualtrics and includes questions about mental and physical activity as well as symptoms. *Time point collected: Daily through 7-days post return to play*.

**Participant Satisfaction**: The participant will be asked to complete a questionnaire regarding his/her satisfaction with the rehabilitation sessions and the intervention. This measure is adapted from the PSQ-18 which is a publicly available scale that measures general athlete satisfaction with care. The PSQ-18 was designed based on feedback from athletes using input from providers about the care they receive and has been used in various settings. *Time point collected: 7 days post return to play*.

**Concussion Injury Index**: This form documents all aspects of a participant's concussion. It is completed by the clinical research staff at the study site. Information gathered on this form includes: sport at time of injury, number of years playing sport, date and time of injury, date reported injury, loss of consciousness, etc. *Time point collected: This form is to be completed over the course of the injury and should be finalized by the 1-month post-return to play time point*.

**Recovery Tracking**: A recovery tracking form documents all aspects of a participant's recovery from a concussion. It is completed by the clinical research staff at the site throughout the time it takes the participant to recover. Length of symptoms, medication usage, therapies/treatments, psychiatric issues, and return to play information will be reported. It also includes information on completion or discontinuation of the study treatment activities (e.g., discontinuation of the intervention for medical reasons). *Time point collected*: *This form should be completed over the course of the injury and should be finalized by the time entry is completed for the 1-month post-injury assessment*.

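### Finding no predictors of attrition is read as random missingness and ends imputation, but a null search among 20–60 leavers cannot show that

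*Protocol article*

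**What the plan says.** All of this is in the protocol article.

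- **Predictor search** (Planned Data Analysis, Specific Aim 1): "We will also assess potential predictors of attrition (e.g., gender, race, socioeconomic status"). The list is introduced as examples.
- **Rule on imputation** (same paragraph): "If no predictable patterns are observed for missing data (i.e., missingness occurs at random), no imputations will be conducted".
- **Weights** (next sentence, no condition attached): "Inverse probability of attrition weights based on the factors influencing attrition will be used to account for potential selection bias due to attrition".
- **Models** (same section): Cox regression for the two primary endpoints. For the secondary endpoints, "recovery trajectories will be examined by use of General Linear Mixed regression models and non-parametric smoothers".
- **Expected loss** (Participants and Eligibility Criteria): "We anticipate ~10–15% attrition due to study demands and seasonal nature of sport through full clearance to return to sport". For the later assessment, "we expect 20–30% attrition for the 1-month timepoint".
- **Sample** (same section): enrolment is "estimated to be 3,500 at baseline and 100–200 in each study arm", that is 200–400 injured athletes in total.
- **Data held before dropout** (Study Outcomes and Assessments): "All concussed participants complete a daily activity and symptom tracking survey". Symptom severity is also measured at 24–48 h.

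**The concern.** The rule is stated outright, so it is not a gap left for a fuller plan to fill. It has three weaknesses.

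1. **The inference is wrong.** Missing at random allows loss to depend on observed factors. Absence of any association with observed factors is what missing completely at random would look like. Failing to see a pattern proves neither.
2. **The weights rest on the same search.** If no influencing factor is identified, the weights are constant. The primary Cox models then rely on ordinary censoring, with loss assumed unrelated to recovery.
3. **The named factors sit away from the expected causes.** The examples are gender, race and socioeconomic status. The eligibility section attributes loss to study demands and season. Session demands before the asymptomatic date differ by arm: the MDR section asks for about four sessions a week once symptoms are stable, whereas EGE session logs begin at Stage 2, after the athlete is asymptomatic.

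At stake is the primary comparison. If slow recoverers leave more often in one arm, that arm's recovery looks faster than it was, and a null predictor search would be reported as reassurance.

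**Working it through.** **The plan's own figure.** The article gives no operating characteristic for the predictor search. Its nearest figure is 83% power at 100 per arm for a hazard ratio of 4.5/7. By Schoenfeld's formula, power = Φ(√(events/4) × |ln HR| − 1.96), with two-sided 5% assumed and |ln(4.5/7)| = 0.442:

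- 200 events: 87.8%
- 180 events (10% attrition): √45 × 0.442 − 1.96 = 1.00, so 84.2%
- 170 events (15% attrition): √42.5 × 0.442 − 1.96 = 0.92, so 82.1%

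The stated 83% is therefore consistent with attrition counted as lost events. That covers precision; bias is a separate matter.

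**Number of leavers**

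- Before clearance: 10% × 200 = 20, up to 15% × 400 = 60.
- At 1 month: 20% × 200 = 40, up to 30% × 400 = 120.

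**Chance of missing a 0.5-SD difference between leavers and completers.** The test (two-sided 5%) and the size of the difference are assumptions. z = 0.5 / √(1/leavers + 1/completers), and the miss rate is about Φ(1.96 − z).

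| N | Attrition | Leavers / completers | z | Missed |
|---|---|---|---|---|
| 200 | 10% | 20 / 180 | 2.12 | 44% |
| 200 | 12.5% | 25 / 175 | 2.34 | 35% |
| 200 | 15% | 30 / 170 | 2.53 | 29% |
| 400 | 10% | 40 / 360 | 3.00 | 15% |
| 400 | 12.5% | 50 / 350 | 3.31 | 9% |
| 400 | 15% | 60 / 340 | 3.57 | 5% |

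With an assumed design effect of 1.5 for clustering, the miss rates become 46–59% at N=200 and 17–31% at N=400.

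**Binary predictor.** Two-proportion test; prevalence of 20–50% and the risk ratio are assumed. Example: N=200, 10% attrition, prevalence 50%, risk ratio 2 gives risks of 6.7% and 13.3%, and power of 35%.

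| Leavers | Risk ratio 1.5: missed | Risk ratio 2: missed |
|---|---|---|
| 20–60 (before clearance) | 61–85% | 18–65% |
| 40–120 (1 month) | 25–73% | 1–36% |

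**Possible bias, time to asymptomatic, no true effect.** Everything here is assumed except the overall level of attrition. In rows 1–5, times are Weibull with shape 1.3 and median 7 days, and leavers are censored uniformly over days 2–7. Row 6 uses exponential times with mean 7 days, 10–15% dropout in each arm and 100 per arm. A hazard ratio above 1 means MDR looks faster.

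| Scenario (MDR / EGE attrition) | HR | Type I error |
|---|---|---|
| 12.5% / 12.5%, slowest third | 1.00 | about 5% |
| 15% / 10%, slowest third | 1.05–1.06 | 5–9% |
| 17.5% / 7.5%, slowest third | 1.12 | 11–12% (100 per arm), 17–18% (200 per arm) |
| 17.5% / 7.5%, slowest third, only half leaving before asymptomatic | 1.04–1.05 | 6–8% |
| 15% / 10% to 17.5% / 7.5%, slower half | 1.02–1.05 | 4–7% |
| Equal totals, one arm's dropout 2–3 times as likely in slow recoverers | 1.01–1.03 | 5–7% |

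In the last scenario a test on sex flagged a pattern in 4–6% of runs, which is chance level.

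**The case against.** The best defence is that the sentence is loosely worded and does little harm. Several parts of that stand.

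- **Only imputation is switched off.** A reader might infer that all missing-data handling stops. The text does not say so: the weights sentence carries no condition, Cox models censor leavers without imputing them, and likelihood-based mixed models are valid under missing at random without imputation. What remains is that weights with no factors do nothing.
- **The predictor list is open.** A reader might infer that recovery-driven dropout cannot be detected. That goes too far. Daily and 24–48 h symptoms are collected and could be examined, and the article says the latter will be considered in all analyses. Only dropout tied to later, unobserved recovery is invisible.
- **No significance test is stated.** The miss rates describe an assumed 5% test. At N=400 they are modest for a 0.5-SD difference, and at 1 month detection is better.
- **Attrition is quoted through full clearance**, so loss before the earlier asymptomatic date should be lower than 10–15%. The arm split has no source in the article.
- **Stopping sessions is not the same as losing the outcome.** Site staff complete the recovery form, including return-to-play information and discontinuation of study treatment, so an athlete who stops sessions may still have endpoint dates. Separate adherence analyses are planned.

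These points limit the size of the problem. They do not make a null search evidence of randomness, and they do not give the weights content when no factor is found.

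**Conclusion.** The rule is wrong as stated and should be replaced, as a moderate correction. The error of inference needs no assumption. The weakness of the search is clearest near 200 injured athletes, where it has low to moderate power. At 400 it depends on how strong the predictor is, which the article does not say.

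A reader might go further and conclude that the trial will probably favour MDR spuriously. The article does not support that. In most scenarios tried the hazard ratio moved only to about 1.01–1.05 with near-nominal error. A 15% / 10% split confined to the slowest third gave 1.05–1.06. The 1.12 figure, with 11–18% type I error, needs a 17.5% / 7.5% split, leavers drawn only from the slowest third, and all of them lost before the asymptomatic date. The 1-month outcomes are less exposed to this rule, although their total loss is larger.

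**What to change.** 1. Delete the conditional rule on imputation, together with its parenthesis equating no pattern with random missingness.
2. State that, whatever the predictor search shows, each primary Cox analysis is accompanied by an inverse-probability-of-censoring weighted version from a small prespecified model: for example arm, 24–48 h symptom severity and the most recent daily symptom score. Keep it small: three terms on 20–60 leavers is about 7–20 leavers per term. Adding the four-level cohort (three more terms) gives about 3–10, so include it only if numbers allow.
3. Apply the same factors to the 1-month outcomes.
4. Add one sensitivity analysis for non-random dropout by arm on the primary endpoints, for example a tipping-point analysis that lowers the post-dropout recovery hazard of MDR leavers until the conclusion changes.
5. Report attrition by arm and by reason.

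The cost is revised wording, a little more programming and, as a rule, slightly wider confidence intervals in the weighted analyses (not calculated here). The symptom data and arm are already collected.
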